#### Transthoracic echocardiography

Baseline left ventricular systolic function, expressed as global ejection fraction in percent according to the biplane Simpson method, will be evaluated by echocardiography by the discharging physician. The procedure will be repeated after 3 months by an experienced echocardiography technician blinded to results of the initial examinations. The physician and the technician will be blinded to the intervention group.

#### Heart rate and blood pressure

Heart rate and blood pressure will be measured following a 15-min rest by a digital automatic sphygmomanometer (Omron m6 ac; Omron Healthcare Co, Ltd, Kyoto, Japan) at baseline and at the conclusion of the 3-month intervention. The mean of two successive measurements on each arm will be used.

#### Exercise capacity

For safety reasons, baseline recordings of exercise capacity and muscle endurance will not be performed following the acute event, and absolute values of change in exercise capacity after intervention can therefore not be estimated. The following assessments are being used in standard clinical care for all AMI patients in Sweden and will be conducted at the 3-month follow-up.

#### Symptom-limited bicycle ergometer exercise test

The test-retest reliability of the symptom-limited bicycle ergometer exercise test in patients with AMI included in the SWEDEHEART registry is excellent [34]. This submaximal exercise test will be performed on a bicycle ergometer (Monark ProVO2, Monark, Varberg, Sweden) according to a WHO protocol [35] and will be supervised by qualified physical therapists blinded to the subject intervention group. At rest, while sitting on the bicycle, subjects will be informed of the test protocol and how to rate their perceived exertion level according to the Borg RPE-scale [36] and dyspnea or chest pain according to Borg’s Category Ratio Scale (CR-10) [37]. Heart rate will be registered at rest with a wireless heart rate sensor. Systolic and diastolic blood pressure will be measured in both arms and reported for the arm with the highest value. Initial starting load, 25 W or 50 W, is based on the subject’s exertion history, with an increased in workload of 25 W every 4.5 min [38]. At 2 and 4 min of each workload, heart rate and rating of Borg scales will be registered. At 3 min, systolic blood pressure will be measured. The exercise test will be discontinued upon reaching either 17 on Borg’s RPE-scale or 7 on Borg’s CR-10 scale. Other criteria for discontinuing the test are chest pain, drop in blood pressure, failure to increase heart rate, and dizziness or other discomfort. Exercise duration of the final increment will be noted. If a subject does not complete the full 4.5 min of the final increment, a corrected maximum workload will be calculated using Strandell’s formula [39]: (submaximum workload) + (25 × *n*/4.5), where submaximal workload is the watt level prior to the termination step, and *n* is the number of minutes completed at the watt level of the final increment of exercise. Maximum oxygen uptake (VO_2_max) at highest achieved workload will be estimated with the Ekblom-Bak test (www.gih.se/ekblombaktest).

#### The dynamic unilateral heel-lift and unilateral shoulder-flexion tests

These tests are designed to evaluate muscle endurance and are commonly used in exercise-based cardiac rehabilitation settings and have excellent reliability for patients with CVD [34, 40].

#### Physical activity scales

The Frändin/Grimby activity scale and the Haskell physical activity scale will be used to subjectively measure physical activity level at baseline and follow-up [41, 42].

#### Food frequency questionnaire

All patients will complete a 132-item food frequency questionnaire with questions related to daily food intake and consumption of bilberries and oats before the study [43]. Before and after the intervention, a full 3-day diet record will be performed.

#### Register follow-up

At 1-year following randomization, we will exploratively assess clinical endpoints in all randomized patients using data from the Swedish Coronary Angiography and Angioplasty Registry (SCAAR) with respect to death, new AMI, and new unplanned revascularization.

### Sample size calculation, data management, and statistical analysis

To the best of our knowledge, no previous intervention study of bilberry/oats with LDL cholesterol as an endpoint in AMI patients has been conducted. Required sample size is calculated on the basis of bilberry-specific interventions from four smaller randomized studies in at-risk populations [18], from our pilot study [27], and from the IMPROVE-IT trial [44], which found a clinically relevant LDL cholesterol-lowering effect of − 0.4 mmol/L when adding treatment with a non-statin agent to standard statin lipid-lowering therapy after AMI. We calculated that 189 subjects would be needed in each study arm to provide 90% statistical power to detect a 0.4 mmol/L or greater reduction in LDL cholesterol in the bilberry or the oat treatment group compared to the reference, with a standard deviation of 1.1 mmol/L and a Bonferroni corrected overall 5% two-sided significance (Statistical Solutions Ltd, Cork, Ireland). The correction is due to two primary hypotheses, (1) bilberry group vs. reference and (2) oat group vs. reference. The same number of participants will be enrolled in the combined bilberry and oat treatment group, for a total of 756 patients in the study. In order to allow for an anticipated dropout rate of ~ 15%, we plan to include 900 patients, 225 in each study arm.

Data will be transferred in coded form from the participating centers to Örebro University Hospital, where data management and statistical analyses will be performed. All patients will be assigned an identifying number, recorded in the eCRF together with collected data. A code list connected to patient study numbers with individual Swedish resident personal identification numbers will be kept separately, and secured at the participating clinical centers. At completion of collection, a database with data from the eCRF and national registers will be established. The results will be analyzed according to the intention-to-treat principle; that is, subjects randomized to a given group will be followed and assessed without regard to the diet intervention eventually received. A subject can withdraw from the study at any time, if it is the wish of the subject, or if it is medically indicated, as judged by the investigator. Data collected up to the end of follow-up will be used in the final analysis of the study. If a subject wants to discontinue the study participation, data collected until that time point will be analyzed in the study. For the primary outcome, on the original scale or log scale, as appropriate, linear regression with pre-intervention to post-intervention change as outcome, adjusted for the baseline values, will be conducted. In cases of missing outcome data, multiple imputation (MI) will be used. Ordinal variables will be assessed with a *χ*^2^ test for trend or the Mann-Whitney *U* test, and Pearson’s *χ*^2^ test or Fisher’s exact test, as appropriate, will be used to evaluate differences among proportions.

To assess compliance, we will compare polyphenolic metabolites associated with bilberry and oat intake in blood at baseline and at 3 months. For values that fall below the limits of detection, an estimated concentration of 50% of the detection limit will be used. Explorative analyses of metabolome and microbiota (omics) data, will be conducted at the Department of Biology and Biological Engineering at Chalmers University of Technology. Instrumental analyses of microbiome and untargeted metabolomics will generate raw data in the range of terabytes. OMICs data will be analyzed at a server dedicated for molecular studies linked to sensitive personal data at The Swedish National Infrastructure for Computing (SNIC) using primarily multivariate strategies, incorporating unsupervised principal components analysis–based strategies and supervised PLS and random forest in-house strategies developed at Chalmers University of Technology [45].

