### Randomization

Potential trial participants will receive written information of the study, and they will receive oral information by medical doctors participating in the study. Informed consent shall be obtained by a Good Clinical Practice-qualified medical doctor or research nurse participating in the study. After providing written informed consent, patients who fulfill inclusion criteria and with no exclusion criteria will be randomized according to a computer-generated random-number sequence. Block randomization is performed in a 1:1:1:1 fashion stratified by study center (Fig. 1). The study will be using SMART-TRIAL® (MEDEI ApS, Aalborg, Denmark), a combined password-protected web-based randomization module and eCRF, in each participating hospital, in order to keep the data management and the statistician blind against the study condition as long as the data bank is open. The randomization list remains with SMART-TRIAL for the whole duration of the study. Thus, randomization will be conducted without any influence of the principal investigators, raters or therapists. Patients, investigators, and all medical staff will be blinded to allocation.

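### Holm's step-down would give more power than plain Bonferroni for the two primary contrasts, at the same family-wise 5% and with no extra patients (an improvement, not an error)

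*Protocol article*

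**What the plan says.** The section on sample size, data management and statistical analysis fixes the multiplicity rule in its sample-size paragraph: "a Bonferroni corrected overall 5% two-sided significance". It gives the reason: "The correction is due to two primary hypotheses, (1) bilberry group vs. reference and (2) oat group vs. reference". The size follows from that level: "189 subjects would be needed in each study arm to provide 90% statistical power". The spread assumed for this is "a standard deviation of 1.1 mmol/L", and the effect that the calculation aims at is worded thus: "detect a 0.4 mmol/L or greater reduction in LDL cholesterol in the bilberry or the oat treatment group compared to the reference".

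The Randomization section sets equal allocation: "Block randomization is performed in a 1:1:1:1 fashion stratified by study center". For dropout the plan says: "In order to allow for an anticipated dropout rate of ~ 15%, we plan to include 900 patients, 225 in each study arm".

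The analysis paragraph gives the primary model as "linear regression with pre-intervention to post-intervention change as outcome, adjusted for the baseline values, will be conducted". Neither paragraph names a step-down, hierarchical or closed procedure. The combined bilberry and oat arm is a secondary objective and lies outside the two-hypothesis family.

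**The concern.** Under plain Bonferroni each contrast is held to 0.025 whatever the other shows. Once one contrast is rejected at 0.025, only one hypothesis in the family remains, and it can be tested at the full 0.05 without the family-wise error exceeding 5%. Holm's procedure uses that; single-step Bonferroni does not.

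What is at stake is power for the second claim. The trial tests two supplements against one reference arm. If both work but one works less well, the weaker contrast is the one a fixed 0.025 threshold may miss and a step-down test may detect. The document gives no reason for preferring the single-step form.

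**Working it through.** **Inputs, all from the protocol article.** Two contrasts sharing one reference arm; overall two-sided 5%, so 0.025 each; effect 0.4 mmol/L; SD 1.1 mmol/L; 189 per arm; equal allocation. With equal arms, a shared reference and equal SDs (assumed), the two test statistics have correlation 0.5.

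**Step 1: reproduce the 189.** n per arm = 2 × (z₀.₉₈₇₅ + z₀.₉₀)² × SD² / δ² = 2 × (2.241 + 1.282)² × 1.21 / 0.16, which rounds up to 188. The exact two-sample t-test needs 189, with power 90.0%. At an uncorrected 0.05 the same normal formula gives 159. So the stated number is right and does rest on 0.025 per contrast.

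**Step 2: power per contrast under Bonferroni.** The standardised effect is 0.4 / (1.1 × √(2/189)) = 0.4 / 0.1132 = 3.535. Power = Φ(3.535 − 2.241) = 90.2% (normal approximation, used from here on).

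**Step 3: power under Holm.** For contrast 1,

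Holm power = P(Z₁ > 2.241) + P(1.960 < Z₁ ≤ 2.241 and Z₂ > 2.241),

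with (Z₁, Z₂) bivariate normal, correlation 0.5. For effects 0.4/0.4 the second term is 3.0 points, so each contrast goes from 90.2% to 93.2%. Both claims: 83.6% + 2 × 3.0 = 89.6%. At least one claim: 90.2% + 90.2% − 83.6%, about 96.9% before rounding of the terms, and the same for either procedure because the first step is identical.

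**Step 4: other effect sizes, 189 per arm.** Effects below 0.4 are assumptions, not figures from the document.

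| True effects (mmol/L) | Quantity | Bonferroni | Holm |
|---|---|---|---|
| 0.4 / 0.4 | each contrast | 90.2% | 93.2% |
| | both claims | 83.6% | 89.6% |
| | at least one | 96.9% | 96.9% |
| 0.4 / 0.2 | the 0.4 arm | 90.2% | 90.6% |
| | the 0.2 arm | 31.8% | 41.9% |
| 0.3 / 0.3 | each contrast | 65.9% | 71.3% |
| | both claims | 50.7% | 61.5% |
| 0.4 / 0 | the 0.4 arm | 90.2% | 90.4% |
| | inert arm, false positive | 2.5% | 4.5% |
| 0 / 0 | family-wise error | 4.6% | 4.6% |

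The 0.4/0 and 0/0 rows come from a two-sided simulation with 4 million replicates. The same simulation agrees with the formulas for 0.4/0.4 and 0.4/0.2 to within 0.1 point.

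**Step 5: planned enrolment.** 225 × 0.85 = 191 evaluable per arm. With effects 0.4/0.4, each contrast goes from 90.5% to 93.5%, and both claims from 84.1% to 90.0%.

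**Step 6: intervals.** Any contrast rejected only at Holm's second step has p between 0.025 and 0.05, so its 97.5% confidence interval includes zero. In the 0.4/0.2 case this affects (41.9 − 31.8) / 41.9 = 24% of the weaker arm's rejections.

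**The case against.** The strongest reply is that nothing here is wrong. Bonferroni is valid, it is prespecified, and the sample size reproduces. That stands, so the point is an efficiency suggestion only.

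Second, the word Bonferroni appears only in the sample-size paragraph. Sizing on Bonferroni is compatible with a step-down final test, and an SAP that is not shown may specify one. That also stands: this article states only the single-step correction, but it does not rule out the other.

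Third, Holm has costs. If one supplement is inert and the other works, the inert arm's false-positive rate rises from 2.5% to 4.5%, while the working arm gains almost nothing. Bonferroni also comes with simple matching 97.5% intervals. Both are fair, so a reader should not infer that the plan gives up power for nothing. The error rate does remain within the 5% the plan allows itself.

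Two further inferences are tempting and unsupported. One is that the 90% is misdescribed because power for both claims is 83.6%. The power sentence refers to the bilberry *or* the oat group, which reads as power per contrast, and the document never sets joint success as its target. The other is that oats are the weaker arm. The Background gives a 5–8% LDL reduction for oats but no mean baseline LDL to convert it to mmol/L, the Abstract calls the oat effect well established and the bilberry evidence small-scale, and nowhere are the two ranked.

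**Conclusion.** The point holds as a cheap improvement. At the plan's own design values, Holm adds about 3 percentage points of power per contrast and 6 points for both claims, and nothing for at least one claim. The gain is larger for a contrast with a smaller effect, about 10 points at an assumed 0.2 mmol/L, and negligible if only one supplement works.

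The figures assume equal SDs of 1.1 in all arms, 189 evaluable per arm and a normal approximation. Baseline adjustment may reduce the residual SD; that would change the power levels but not the ordering, because Holm rejects whatever Bonferroni rejects in every data set. No conclusion of the trial is put at risk if the plan stays as it is.

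**What to change.** State, before unblinding, that the two primary contrasts are tested by Holm's procedure at a family-wise two-sided 5%: the smaller p at 0.025 and, only if that is rejected, the other at 0.05. Keep 189 per arm and 900 in total.

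Fix the reporting in the same place, in one of two ways:

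- Holm-adjusted p-values for the decision, with 95% confidence intervals described as unadjusted for multiplicity; or
- 97.5% confidence intervals, with an explicit note that they may not match the Holm decision for a contrast rejected at the second step.

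Record that the gain depends on both supplements having an effect, and that an inert arm's false-positive rate can rise towards 5%.

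The cost is a few lines in the protocol or SAP, with no extra patients, visits or data. It has to be prespecified, because a switch made after results are seen would not be credible. If the SAP already specifies a step-down test, it is enough to confirm that.

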### Examinations and blood tests

Subjects will be assessed at baseline, as inpatients, and at 3-month follow-up as outpatients. Examinations and samples will be collected as follows.

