#### Blood and fecal samples

Venous blood samples will be collected at baseline and during intervention week 12. The blood samples will be centrifuged immediately and stored at – 80 °C pending further analyses. Fasting lipid profile [low-density lipoprotein cholesterol (LDL-C); total cholesterol (TC); high-density lipoprotein cholesterol (HDL-C); triglycerides (TG); small dense low-density lipoprotein (sdLDL); oxidized LDL; apolipoprotein A (apo A); apolipoprotein B (apo B); lipoprotein(a) (lp[a]); inflammatory markers high-sensitivity C-reactive protein (hs-CRP) and interleukin 6 (IL-6); fasting glucose; insulin; creatinine; cystatin C, C-peptide; glycosylated hemoglobin (HbA1c); and the heart function markers troponin-I and N-terminal pro b-type natriuretic peptide (NT-proBNP)] will be analyzed.

Analysis of blood samples will be conducted to assess diet compliance based on the presumption that the concentrations of phenolic acid derivatives will be higher in the bilberry group and avenanthramides and/or avenocosides higher in the oat and combined bilberry/oat groups compared to the reference group [27]. Phenolic acid derivative components associated with bilberry consumption [28] and avenanthramides associated with oats will be analyzed by a validated method combining liquid chromatography with mass spectrometry [29, 30].

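### Medical withdrawal is worded as leaving the study, not only the drink, and the plan does not say whether such patients still give the 3-month outcomes that its intention-to-treat statement promises

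*Protocol article*

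**What the plan says.** All statements are in the Protocol article. Under Sample size calculation, data management, and statistical analysis, the intention-to-treat principle is spelled out as "subjects randomized to a given group will be followed and assessed without regard to the diet intervention eventually received". The withdrawal rule follows directly: "A subject can withdraw from the study at any time, if it is the wish of the subject, or if it is medically indicated". Its last part reads in full "if it is medically indicated, as judged by the investigator". A further sentence says that data gathered to the close of follow-up enter the final analysis. Another covers patients who choose to leave: "If a subject wants to discontinue the study participation, data collected until that time point will be analyzed in the study". For gaps, "In cases of missing outcome data, multiple imputation (MI) will be used".

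On timing, Examinations and blood tests says "Subjects will be assessed at baseline, as inpatients, and at 3-month follow-up as outpatients", and Blood and fecal samples says "Venous blood samples will be collected at baseline and during intervention week 12". Exercise capacity explains that no baseline test is done for safety reasons, and adds "The following assessments are being used in standard clinical care for all AMI patients in Sweden and will be conducted at the 3-month follow-up". The 1-year register follow-up covers all randomized patients, but only for death, new AMI and unplanned revascularization.

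**The concern.** A medical reason may justify stopping a beverage. It does not by itself justify forgoing a blood sample. The intention-to-treat sentence says that assessment goes on regardless of diet, while the next sentence describes the medical exit as an exit from the study. Sites could reasonably act on either.

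The ambiguity matters more here than in a trial with repeated visits. Nothing is measured between baseline and the end of the intervention, so a patient who leaves early has a baseline LDL and nothing after it, and no exercise result at all. If medically withdrawn patients are not assessed, the data may contain few or no off-drink LDL values from which an imputation model could learn what happens after stopping. The reported result would then lean toward the effect in people who kept drinking, under an intention-to-treat label. An outcome that was never collected cannot be restored by the analysis plan.

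**Working it through.** **1. The plan's own sample size.** Inputs from the sample size section: difference 0.4 mmol/L, SD 1.1 mmol/L, 90% power, two-sided 5% split over two hypotheses (0.025 each).

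- Normal approximation: n = 2 × (2.241 + 1.282)² × 1.1² / 0.4² = 188 per arm.
- Noncentral t: power is 0.8984 at 188 and 0.9000 at 189, so the stated 189 reproduces.
- Dropout: 189 / 0.85 = 223 per arm. The planned 225 tolerates 1 − 189/225 = 16% loss.

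**2. Is it a power problem?** Power (normal approximation) with 225 per arm, by share without a week-12 LDL:

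| Share missing | Observed per arm | Power |
|---|---|---|
| 0% | 225 | 94.7% |
| 10% | 202.5 | 92.2% |
| 15% | 191 | 90.6% |
| 20% | 180 | 88.7% |

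At the anticipated loss of about 15% the trial keeps its 90%. Power is not where the harm lies.

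**3. What is observed for a patient who leaves before week 12 and is not assessed again?**

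| Outcome | Baseline | In between | Week 12 / 3 months |
|---|---|---|---|
| LDL (primary) | yes | none scheduled | missing |
| Exercise capacity (major secondary) | not tested | none scheduled | missing |
| Register events at 1 year | – | – | available, but not LDL or exercise |

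**4. What could this do to the LDL estimate?** The documents give no rate of medical withdrawal and no imputation model, so this is an illustration. Assumptions: a share f of an active arm leaves on medical grounds and has no remaining effect at week 12; the others have the planned 0.4 mmol/L; imputation within arm draws on patients who stayed and so returns about 0.40.

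Effect in all randomized = (1 − f) × 0.4.

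| f | All-randomized effect | Completer-based imputation | Difference |
|---|---|---|---|
| 5% | 0.95 × 0.4 = 0.38 | about 0.40 | 0.02 |
| 10% | 0.90 × 0.4 = 0.36 | about 0.40 | 0.04 |
| 15% | 0.85 × 0.4 = 0.34 | about 0.40 | 0.06 |

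The last row treats the whole dropout allowance as medical withdrawal with no residual effect, so it is near a worst case within that allowance.

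**The case against.** The other side has a good deal to say.

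- A reader might infer that the plan has no place for a patient who stops the drink but stays in the study. The text does not support that. The intention-to-treat sentence implies such a place, and the Discussion expects non-adherent patients to be in the trial, since it measures compliance from returned packages and unused drinks.
- A reader might infer that data are cut off for every medical withdrawal. The cut-off sentence covers only subjects who want to discontinue. The sentence about data up to the end of follow-up could mean that medically stopped patients are still assessed. It could also mean the opposite, and that open reading is what remains of the concern.
- That the investigator may remove a patient who has not asked to leave is also an inference. The wording is that the subject can withdraw.
- That exercise capacity would be analyzed only in those who stayed is not stated. The imputation sentence is not limited to LDL.
- An overstatement of 0.06 mmol/L (0.06/0.34 = 18%) cannot be presented as expected. The roughly 15% dropout is not split by cause, and those who withdraw consent stay missing under any wording.
- Stopping that differs by arm because of fiber content (Table 3) is conceivable, but the article does not document it. It expects no negative side effects.
- The imputation model and detailed discontinuation procedures may well be in the full protocol or the analysis plan. Their absence from an article is no fault.

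What stands is narrower. The article does state a withdrawal rule, words it as leaving the study, and places it beside a promise of continued assessment without saying which governs.

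**Conclusion.** The concern holds as a conflict between stated sentences that leaves outcome collection after medical withdrawal open. A patient withdrawn before the week-12 sample and the 3-month test, and not assessed afterwards, contributes no observed primary or major secondary outcome. The register does not recover either one. Multiple imputation keeps the patient in the analysis, but would normally rest on baseline data and on those who stayed.

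The consequence is possible bias toward the on-drink effect and an unclear target of estimation, not an undersized trial. Its size is unknown. The illustrative range of 0.02 to 0.06 mmol/L rests on assumed withdrawal shares of 5% to 15%, no residual effect after stopping, and imputation from completers. It should not be read as a forecast. The point deserves correction because the remedy is cheap and missed measurements cannot be retrieved later.

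**What to change.** Reconcile the sentences in the statistical analysis section by distinguishing two events:

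1. **Stopping the drink**, for any reason. The clinical decision to stop is unchanged. The patient stays in the study.
2. **Withdrawing consent to follow-up.** Only this ends outcome collection.

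Unless consent to follow-up is withdrawn, the week-12 fasting LDL sample is still sought, as are those 3-month assessments that the treating clinicians consider feasible. In Blood and fecal samples, time the sample from randomization rather than by intervention week, so that it plainly applies to patients no longer taking the drink. Record the date of, and reason for, the last drink, and include these outcomes in the intention-to-treat analysis.

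The cost is protocol wording, an eCRF entry and an instruction to sites. No visit is added: the 3-month visit is already scheduled, and the article describes the exercise tests as standard care. The downside is a little site work and a possibly slightly smaller estimated effect, because patients who stopped are counted with their actual values.

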### Study population and patient selection

Subjects in this multicenter study will be recruited from among patients referred to Sahlgrenska University Hospital Gothenburg, Umeå University Hospital, Lund University Hospital, Västerås general hospital, Karlstad general hospital, and Örebro University Hospital for coronary angiography/PCI due to ST-segment elevation myocardial infarction (STEMI) or non-ST-segment elevation myocardial infarction (NSTEMI). STEMI is defined as chest pain suggestive of myocardial ischemia for at least 30 min prior to hospital admission with time from onset of symptoms less than 24 h, an ECG with new ST-segment elevation in two or more contiguous leads of ≥ 0.2 mV in leads V2–V3 and/or ≥ 0.1 mV in other leads, or a probable new-onset left bundle branch block. NSTEMI is defined as a combination of onset of symptoms such as central chest pain or aggravated angina pectoris, with or without ECG changes, with ST-segment depression or an inverted T-wave and rise and/or fall of troponin-T or troponin-I above the established margin of an AMI. Study inclusion and exclusion criteria are defined in Table 2.

**Table 2 Tab2:** Inclusion and exclusion criteria

Inclusion criteria • STEMI or NSTEMI • Completed coronary angiography/PCI • Male and female subjects ≥ 18 years • Allocated to atorvastatin at a daily dose of 80 mg • Written informed consent Exclusion criteria • Emergency coronary artery bypass grafting • < 18 years of age • LDL cholesterol < 2.0 mmol/L • Daily intake or the intent to initiate daily intake of bilberry in any form or daily intake of > 15 g of oatmeal or equivalent • Previous randomization in the BIOAMI trial • Inability to provide informed consent	

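### Study centre stratifies the randomization but is not in the stated primary model; adding it recovers a modest amount of precision, and mmol/L should be named as the primary scale

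*Protocol article*

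**What the plan says.** The Randomization section of the Protocol article states: "Block randomization is performed in a 1:1:1:1 fashion stratified by study center". The section on study population and patient selection names six recruiting hospitals: "Sahlgrenska University Hospital Gothenburg, Umeå University Hospital, Lund University Hospital, Västerås general hospital, Karlstad general hospital, and Örebro University Hospital".

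The section on sample size, data management and statistical analysis gives the primary model as "linear regression with pre-intervention to post-intervention change as outcome, adjusted for the baseline values, will be conducted". Baseline is the only adjustment named, and no other analysis statement in the article mentions centre. The sentence opens with the choice of scale: "For the primary outcome, on the original scale or log scale, as appropriate". It gives no default scale and no rule for choosing.

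The same section sets the power target on the original scale. The trial is sized "to detect a 0.4 mmol/L or greater reduction in LDL cholesterol in the bilberry or the oat treatment group compared to the reference". The planning SD is also in mmol/L (1.1), and the two-sided 5% level is divided between the two primary comparisons by Bonferroni.

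**The concern.** Blocking within centre makes the arms nearly equal in size at every hospital, so differences between hospitals largely cancel out of the treatment contrast. A model without centre does not credit this. It leaves the between-centre variation in the residual and reports a standard error that includes it. The usual principle is to analyse by the factors used to randomize. Here the only stated stratification factor is absent from the stated adjustment set. What is at stake is efficiency in the two primary comparisons: confidence intervals a little wider, and p-values a little larger, than the design warrants.

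The open scale raises a separate, smaller matter. A regression on the log scale estimates a ratio, while the sample size was set for an absolute difference. A fixed difference is not a fixed ratio: 0.4 mmol/L is 20% of 2.0 mmol/L (the level below which patients are excluded) and a smaller percentage of any higher value. A primary result on the log scale would therefore not directly address the effect for which the trial was sized.

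**Working it through.** **Inputs from the Protocol article.** Difference 0.4 mmol/L; SD 1.1 mmol/L; 189 per arm; power 90%; two primary hypotheses sharing a two-sided 5% by Bonferroni, so 0.05/2 = 0.025 per test (critical value 2.2414); six centres.

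**Input assumed.** r, the share of residual variance due to centre after baseline adjustment. The documents do not give it; the range shown is 0 to 0.10. The SD of 1.1 is taken as the residual SD with centre variation included.

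**Step 1: reproduce the planned size.** n per arm = 2 × (2.2414 + 1.2816)² × (1.1/0.4)² = 2 × 12.41 × 7.5625 ≈ 187.7, so 188 by the normal approximation. With the noncentral t distribution, 189 gives power 0.9000. The stated 189 is confirmed.

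**Step 2: standard errors with and without centre.**
- Reported without centre: 1.1 × √(2/189) = 0.1132.
- Actual, with arms balanced within centre: 0.1132 × √(1 − r).
- Ratio of reported to actual: 1/√(1 − r).

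**Step 3: consequences.**
- Actual per-test alpha without centre: 2 × [1 − Φ(2.2414/√(1 − r))].
- Standardized effect at r = 0: 0.4/0.1132 = 3.535.
- Power without centre: Φ((3.535 − 2.2414)/√(1 − r)).
- Power with centre: Φ(3.535/√(1 − r) − 2.2414).

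| r (assumed) | SE too large by | Actual alpha (nominal 0.025) | Power without centre | Power with centre |
|---|---|---|---|---|
| 0 | 0% | 0.0250 | 90.2% | 90.2% |
| 0.01 | 0.5% | 0.0243 | 90.3% | 90.5% |
| 0.02 | 1.0% | 0.0236 | 90.4% | 90.8% |
| 0.05 | 2.6% | 0.0215 | 90.8% | 91.7% |
| 0.10 | 5.4% | 0.0181 | 91.4% | 93.1% |

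At r = 0.10, for example, 1/√0.90 = 1.054. Power without centre is Φ(1.2935 × 1.054) = Φ(1.363) = 0.9136. Power with centre is Φ(3.726 − 2.2414) = Φ(1.485) = 0.9312. The difference is 0.0176, or 1.7 to 1.8 points depending on rounding.

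**Step 4: simulation check.** The setting was 756 patients, six equal centres and blocks of 8 (centre and block sizes assumed), with 8,000 null trials per value of r and 4,000 under the alternative.
- r = 0.10, without centre: mean reported SE 0.1133 against an empirical SD of the estimate of 0.1061; null rejection 0.016.
- r = 0.10, with centre: mean reported SE 0.1074; null rejection 0.022.
- r = 0.05, power: 90.7% without centre, 91.7% with it.
- r = 0: no difference between the two models.

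The simulation error of a rejection rate near 0.025 is √(0.025 × 0.975/8000) = 0.0017. The differences in alpha expected at r = 0.02 and below are too small for this simulation to resolve; there the formula is the guide.

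**The case against.** The strongest objection is scope. This is a journal article condensing a fuller protocol, and an analysis plan may exist. Full covariate lists and transformation rules are often left to such documents, and the article nowhere says that centre will be ignored. Part of this stands: an unseen document may already include centre and fix the scale. But the article does state an outcome, a model and an adjustment set, and that set lacks the only stratification factor. If centre is added elsewhere, the sentence as printed no longer describes the primary analysis.

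The second objection is size, and it stands. The centre share is assumed. All patients are to receive the same statin dose, which removes one possible source of centre differences. In every row of the table the analysis without centre still exceeds 90% power. A reader might infer that the error bars will certainly be wrong, or that the trial is underpowered. The documents support neither: the first depends on a centre effect they do not report, and the second is contradicted by the table.

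A reader might also infer that the open scale gives two attempts at each primary test. In null simulations with 189 per arm and assumed LDL distributions, keeping the smaller of the two p-values raised the per-test error to about 3.1%. Choosing the scale from the skewness of pooled residuals, without treatment labels, gave 2.4 to 2.6%, which is no material inflation. The text does not say that both tests will be run and the better one kept. Its ordinary meaning is a choice on distributional fit. The Randomization section also keeps the statistician blind while the database is open, although it does not say when the scale is chosen. The type I error claim is therefore not made here.

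**Conclusion.** The point holds as a modest matter of efficiency and of matching the analysis to the design. For an assumed centre share of 0 to 10% of residual variance, leaving centre out makes standard errors 0 to 5.4% too large, lowers the actual per-test alpha from 0.025 to no less than 0.018, and forgoes at most 1.8 points of power. The error is on the conservative side. If centre does not predict LDL change after baseline adjustment, nothing is lost. The figures rest on the planned SD of 1.1 mmol/L, 189 evaluable patients per arm, and near-balance of arms within centres.

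On the scale, only the narrow point survives: a log-scale ratio is a different estimand from the 0.4 mmol/L difference used for sizing, and the article does not say which is primary.

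**What to change.** State the primary analysis as a linear regression of LDL change in mmol/L on treatment arm, baseline LDL and study centre, with centre as a fixed effect with six levels. Name the log-scale model as a sensitivity analysis only.

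The cost is one sentence and five degrees of freedom. With 756 evaluable patients, the model without centre has five parameters (intercept, three arm terms, baseline) and 751 residual degrees of freedom; with centre it has 746. The sample size need not change. If a fuller protocol or analysis plan already specifies centre and the mmol/L scale, the published description need only be brought into line with it.
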